## Methods and analysis

### Study design

This is a multicentre, open-label, randomised controlled clinical trial conducted across 39 hospitals in Spain. Participants will be randomised in a 1:1 ratio to undergo EST or expectant management. Given the nature of the intervention, blinding is not feasible; however, objective outcomes will mitigate bias.

#### Concomitant care

Both groups may receive complementary medical treatment at the discretion of the treating specialist, in accordance with the clinical protocols of each participating centre. In most cases, such treatments will already have been prescribed before study entry.

### Participants

Eligibility criteria are listed below

#### Inclusion Criteria

Female sexAge ≥18 and ≤45 yearsUltrasound suspicion of unilocular endometrioma or with a thin septum less than 3 mmSize between 30 and 100 mm, persistent for at least 3–6 months since diagnosisCa125 marker < 300 UI/mL and HE4 < 70 pMBilateral endometriomas.Recurrent endometriomasPrevious ovarian intervention, including ovarian surgery or sclerotherapySigned informed consent

#### Exclusion Criteria

Age <18 or >45 yearsHistory of ovarian or uterine cancerEndometrioma size < 30 mm or >100 mmIndication for surgical treatment of the endometrioma due to suspected severe extra-ovarian endometriosis or any other cause. In cases of clinical suspicion of severe extra-ovarian endometriosis, pelvic MRI will be performed to assess disease extent and confirm eligibility.Ultrasound suspicion of dermoid cysts, anechoic cysts, or cysts with high risk of malignancyCa125 > 300 UI/mLHE4 > 70 pMPregnant womenPatients who do not wish to participate in the study or who are mentally incapacitated

All participant centers are members of the ESCOMA team. The list of participating Hospitals is shown in the Supplementary Appendix S1.

### Interventions

Intervention group: Ultrasound-guided ethanol sclerotherapy (EST).

#### Procedure

Analgesic treatment is administered before the procedure, consisting of ibuprofen 1 h before and diazepam ½ hour before. On the day of the puncture, the patient must not present purulent leucorrhoea or genital bleeding.A single puncture is performed, preferably via the vaginal route, although an abdominal approach may be used if required by the patient's condition or by the cyst's characteristics, for example in virginal patients or when marked vascularization is observed along the puncture pathway.The abdominal wall or vaginal canal is disinfected with a povidone–iodine solution.A sterile 17-gauge needle (BD Medical Franklin Lakes, NJ, Becton, Dickinson and Company) is used. Under ultrasound guidance, the needle is advanced into the centre of the cyst and connected, through an extension tube and a three-way stopcock, to a vacuum aspiration system.Aspiration of the endometrioma contents may require dilution with saline solution (SS) when the fluid is thick. The aspirated fluid is measured using a syringe or an adapted measurement system.After nearly complete aspiration, several washes with Saline solution (SS) are performed until clear fluid is obtained.A volume of 100% ethanol equivalent to two-thirds of the aspirated volume is then instilled into the cyst, without exceeding 100 mL.The ethanol is left in place for 15 min without moving the needle, which remains inside the cyst.Subsequently, the cyst is emptied and washed twice with SS, using the same volume as the instilled ethanol.The aspirated fluid is sent to the pathology department for cytological examination to confirm the absence of atypical cells.The 100% ethanol solution used at all participating centres will be identical. The product will be supplied by *Farmacia Carreras*, the authorized provider for hospitals throughout Spain, ensuring consistency and avoiding potential bias related to variations in preparation.

#### Expectant management group

Participants will continue the treatment they were receiving before study inclusion, or no treatment if none was previously prescribed. During follow-up, medical treatment may be initiated or modified according to clinical circumstances, patient preference, and usual clinical practice. Recommendations are provided to investigators to promote consistency in the management of the expectant-management group across participating centres (Supplementary Appendix 3); however, treatment decisions are not mandated by the study protocol. All concomitant treatments and subsequent changes will be prospectively recorded in the study database. Analgesia and supportive care are permitted in both groups. To minimize potential imbalance in this relevant clinical factor, randomisation will be stratified according to the presence or absence of concomitant hormonal treatment at study inclusion. In addition, the potential effect of hormonal treatment received during follow-up will be accounted for in the statistical analysis, including appropriate adjusted and sensitivity analyses.

### Outcomes

Primary outcome: Quality of life assessed with the EHP-5 questionnaire, a validated self-administered patient-reported outcome measure, at baseline and 6 months.

#### Secondary outcomes

Pain reduction (VAS score at 6 months and time to improvement)Changes in pain-associated biomarkers in serum (cortisol, CRP, IL-6) and urine (cortisol, adrenaline, noradrenaline)Ovarian reserve markers (AMH and AFC)Reduction in cyst size (largest diameter)Reproductive outcomes (spontaneous pregnancies, ART pregnancies, number of ART cycles, oocyte yield),Adverse events and complications,Number of misdiagnosed cysts (non-endometrioma)Treatment-related direct medical costs from the healthcare system perspective.Endometrioma recurrence or progression.

Long-term outcomes assessed during follow-up up to 24 months will include endometrioma recurrence or progression, subsequent interventions, and reproductive outcomes among women with pregnancy desire, including spontaneous pregnancies and ART-related outcomes (number of ART cycles, number of oocytes retrieved, and pregnancies achieved through ART).

A detailed description of all secondary outcomes, including definitions, timing and methods of aggregation, is provided in Supplementary Table S1.

### Sample size

For the primary endpoint (quality of life), the sample size was estimated based on published data reporting an improvement in quality of life—considering patient-reported pain—of approximately 55.25% (range 53%–60%) after conservative management and 71.5% (range 63%–80%) after EST. Assuming a two-sided *α* of 0.05 and a statistical power greater than 0.80, 144 participants per group are required to detect a statistically significant difference between the two proportions (p_1_ = 0.5525 and p_2_ = 0.715). Considering a 5% loss to follow-up, the total sample size will be 288 participants (144 per group). Calculations were performed using the arcsine (arcsin–square-root) approximation for comparison of proportions.

For the fertility substudy (subgroup of women expressing a desire for pregnancy), published data indicate pregnancy rates of approximately 48% after EST (range 37%–55%) and 15% with conservative management. Assuming a two-sided *α* of 0.05 and a *β* of 0.20 (power = 0.80), 33 participants per group are required to detect this difference (p_1_ = 0.48, p_2_ = 0.15). Allowing for a 10% loss to follow-up, the final target will be 37 participants per group, yielding a total of 74 women for the fertility analysis.

These calculations ensure adequate statistical power to detect clinically meaningful differences in both quality of life and reproductive outcomes between treatment groups.

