**Methods and analysis:**

ESCOMA is a prospective, multicentre, randomised controlled trial comparing ultrasound-guided ethanol sclerotherapy with expectant management. A total of 288 women with ovarian endometriomas will be randomised in a 1:1 ratio. The primary outcome is change in quality of life at 6 months, assessed using the Endometriosis Health Profile-5 (EHP-5). Secondary outcomes include pain reduction, changes in pain-related biomarkers, ovarian reserve markers, cyst size reduction, reproductive outcomes, adverse events and complications, diagnostic accuracy, and healthcare costs. Analyses will be performed according to both intention-to-treat and per-protocol principles.

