### Statistical analysis

Primary analysis will use mixed linear regression models with clustering by patient to compare QoL scores. Secondary analyses will include chi-square for categorical outcomes, repeated measures ANOVA, Kaplan–Meier survival curves for pregnancy rates, and Mann–Whitney U tests for oocyte counts. Analyses will be performed on both intention-to-treat and per-protocol populations. A statistical analysis plan will be finalised prior to database lock.

Secondary outcomes will be analysed as defined in Supplementary Table S1. Continuous outcomes (e.g., VAS, AMH, AFC, cyst diameter, oocyte yield, biomarker levels) will be compared between groups using appropriate parametric or non-parametric tests depending on distribution. Categorical outcomes (e.g., pregnancy rates, adverse events, misdiagnosis) will be compared using *χ*^2^ or Fisher's exact test. Time-to-event outcomes (e.g., time to clinical improvement, time to spontaneous pregnancy) will be analysed using Kaplan–Meier curves and log-rank tests. Effect estimates will be presented with 95% confidence intervals. A detailed Statistical Analysis Plan is provided in the Supplementary Appendix S7.

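### The power stated for the primary endpoint belongs to a comparison of two proportions, not to the planned mixed-model comparison of EHP-5 scores

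*Protocol article*

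**What the plan says.** **Outcome.** The Abstract (Methods and analysis) states: "The primary outcome is change in quality of life at 6 months, assessed using the Endometriosis Health Profile-5 (EHP-5"). The Primary objective and Outcomes sections agree, with assessments at baseline and 6 months. None of these sections gives a cut-off that would classify a woman as improved.

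**Analysis.** The Statistical analysis section states: "Primary analysis will use mixed linear regression models with clustering by patient to compare QoL scores".

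**Sample size.** For the primary endpoint, the Sample size section starts from "published data reporting an improvement in quality of life—considering patient-reported pain—of approximately 55.25% (range 53%–60%) after conservative management", against 71.5% (range 63% to 80%) after sclerotherapy. At a two-sided α of 0.05 and power above 0.80, it concludes that "144 participants per group are required to detect a statistically significant difference between the two proportions" (p1 = 0.5525 and p2 = 0.715). The method is named: "Calculations were performed using the arcsine (arcsin–square-root) approximation for comparison of proportions". The total of 288 is said to allow for 5% loss to follow-up. The section closes by asserting that its calculations secure adequate power for clinically meaningful differences in quality of life as well as in reproductive outcomes.

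**The concern.** The sample-size calculation and the primary analysis differ in scale (binary against continuous) and in test (two proportions against a mixed linear model). They also differ, at least in part, in what is measured. The published rates are described as quality-of-life improvement seen through patient-reported pain, whereas the protocol treats pain on a visual analogue scale as a separate secondary outcome. The rates are not said to have been measured on EHP-5.

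What is at stake is the justification for the primary comparison. As written, the article does not say what EHP-5 difference the trial was designed to detect, so the observed effect cannot be set against a planned one. The closing assurance about power for quality of life has nothing under it for the analysis that will be run. This is not a detail that an article leaves to the statistical analysis plan: the sizing basis and the primary model are both stated, and they do not match.

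**Working it through.** **Inputs from the protocol article**
- Sample size: two-sided α = 0.05, power above 0.80, p1 = 0.5525, p2 = 0.715, arcsine method, 5% loss, 144 per group.
- Study design: 1:1 allocation.
- Not given: EHP-5 mean difference, SD, or correlation between baseline and 6 months.

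**1. Reproducing the stated figure**
- h = 2·arcsin(√0.715) − 2·arcsin(√0.5525) = 0.3393.
- n = 2(1.960 + 0.842)² / h² = 136.4, so 137 per group.
- Allowance for 5% loss: 137 × 1.05 = 143.9, so 144. (Dividing instead, 137/0.95 gives 145.)
- Power of the two-proportion test by the arcsine method: 0.82 at 144 per group and 0.80 at 137.

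The 144 and the power above 0.80 are therefore right for a two-proportion test. The text calls 144 the number required and also the number after loss; it matches only the second.

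**2. What the same numbers give for a comparison of mean scores**

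Evaluable per group: 144 × 0.95 = 136.8, about 137.

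Detectable standardised difference at 80% power, without baseline adjustment: (1.960 + 0.842) × √(2/137) = 0.34 SD.

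Power ≈ Φ(d × √(137/2) − 1.960), for assumed values of d:

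| d (SD units, assumed) | Power |
|---|---|
| 0.20 | 0.38 |
| 0.25 | 0.54 |
| 0.30 | 0.70 |
| 0.40 | 0.91 |
| 0.44 | 0.95 |

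This is a sensitivity table. The article gives no EHP-5 effect that would pick out a row.

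**3. Linking the proportions to a score (assumption)**

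Suppose that improvement were a single common cut on a normally distributed score with equal SD in both groups. Then:
- d = Φ⁻¹(0.715) − Φ⁻¹(0.5525) = 0.436 SD.
- Evaluable number for 80% power: 2 × (2.802/0.436)² ≈ 83 per group.
- Power at 137 per group: about 0.95.

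**4. Effect of baseline adjustment (assumption)**
- If the model adjusts for baseline and the baseline to 6-month correlation is r = 0.5, the detectable difference is 0.34 × √(1 − 0.5²) = 0.29 SD.
- If the model compares unadjusted change, the variance is 2(1 − r)σ², which equals σ² at r = 0.5. The detectable difference stays at 0.34 SD.

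The article does not say which of these its mixed model does.

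**The case against.** The strongest reply is that nothing here shows the trial to be too small. On the only effect the article supplies, the conversion in step 3 gives 0.44 SD and about 95% power, so sizing on proportions would be conservative for an analysis of scores. That stands. It makes this a defect in the justification, not a demonstrated shortfall in patients. It does not make the stated figure apply, because the conversion rests on assumptions that the article does not make.

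Three stronger readings are tempting, and the document does not support them:
- **True power lies between about 40% and 95%.** The low end comes from choosing d = 0.20, and nothing in the article points to an effect that small. The high end is only the normal-score conversion; it is not an upper bound. Power varies with the assumed effect in every trial.
- **A null result could not be interpreted.** The Statistical analysis section says that effect estimates will carry 95% confidence intervals, and a null result can be read from its interval. What is missing is a planned EHP-5 difference to read it against.
- **The rates are simply pain data.** The article calls them quality-of-life improvement in the light of patient-reported pain. The cited sources are not at hand, so no more can be said.

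It is also fair to say that an EHP-5 responder definition may exist in the supplementary analysis plan, which is not shown. The supportable statement is that the article gives none. Even if one exists there, the primary analysis stated in the article would still be a comparison of scores.

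**Conclusion.** The point holds in a limited form. The stated power above 0.80 at 144 per group is arithmetically correct for comparing 55.25% with 71.5%, but that is not the stated primary analysis. The assurance of adequate power for quality of life is therefore unsupported as written.

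A reader might infer that the trial is underpowered; the document does not show this. With 137 evaluable per group and no baseline adjustment, 80% power is reached at 0.34 SD. Power is lower for smaller true differences, and about 95% at the 0.44 SD implied by the normal-score assumption. Which case applies cannot be settled from the article, because it gives neither an EHP-5 difference nor an SD.

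**What to change.** Keep 288 participants and replace the primary-endpoint paragraph in the Sample size section with a statement for the analysis that will be run. For example: about 137 evaluable women per group (144 less 5%) give 80% power, at two-sided 0.05, to detect a between-group difference of 0.34 SD in EHP-5 at 6 months. The figure of about 0.29 SD may be added only if the model adjusts for baseline, with the correlation of 0.5 labelled as an assumption.

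Convert the detectable difference to EHP-5 points with a cited SD, and compare it with a cited minimal important difference. Without both, a detectable difference worked back from a fixed sample size justifies little.

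Delete the two-proportion calculation as the basis for the primary endpoint. Moving it to an EHP-5 responder outcome would repeat the mismatch, because the rates are not stated to come from EHP-5. Remove or qualify the closing assurance of adequate power as it concerns quality of life.

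Cost: one recalculation and a rewritten paragraph, with no extra participants. The stated figure may look less favourable than the present one. The change is best made before outcome data are seen.

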## Strengths and limitations of this study

First multicentre randomised clinical trial directly comparing ethanol sclerotherapy and expectant management for ovarian endometriomas.Primary outcome focused on quality of life, assessed with a validated and widely used tool (EHP-5).Inclusion of ovarian reserve markers and reproductive outcomes (pregnancy rates and time to conception) enhances the clinical relevance of the study; however, fertility outcomes will only be evaluated in the subgroup of women who express a desire for pregnancy, which reduces the sample size for these endpoints and may limit the statistical power to detect differences between groups.The additional assessment of healthcare costs provides valuable information on the health-economic impact of both treatment strategies.Although an open-label design may influence subjective outcomes such as quality of life, objective biomarkers and pregnancy outcomes are less susceptible to bias.

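### Fertility sample size: 33 per group is not the arcsine result and appears to contain the 10% loss that is then added again, and the unconditional power claim conflicts with the stated limitation

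*Protocol article*

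**What the plan says.** The Sample size section of the protocol article has two calculations.

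- **Primary endpoint.** Proportions 0.5525 and 0.715, two-sided 5%, power above 80%. The text gives 144 per group as required, then considers a 5% loss and again arrives at 144 per group (288 in total). The paragraph closes with: "Calculations were performed using the arcsine (arcsin–square-root) approximation for comparison of proportions".
- **Fertility substudy.** "published data indicate pregnancy rates of approximately 48% after EST (range 37%–55%) and 15% with conservative management". With two-sided 5% and 80% power, "33 participants per group are required to detect this difference". Then: "Allowing for a 10% loss to follow-up, the final target will be 37 participants per group, yielding a total of 74 women".

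The section ends: "These calculations ensure adequate statistical power to detect clinically meaningful differences in both quality of life and reproductive outcomes between treatment groups".

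The Strengths and limitations section says that fertility outcomes are assessed only in women who want a pregnancy, "which reduces the sample size for these endpoints and may limit the statistical power to detect differences between groups". The limitations paragraph of the Discussion repeats that the effective sample size is reduced. Under Randomisation and allocation, pregnancy desire is a stratification factor. The eligibility criteria do not require it.

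**The concern.** There are two separate matters.

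First, the 33 does not follow from its own inputs under the named method, and the two paragraphs treat loss differently. In the fertility paragraph the required number is raised for loss. In the primary paragraph the same number stands before and after the loss allowance.

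Second, the article says without condition that power for reproductive outcomes is adequate, and elsewhere says that power for those same outcomes may be limited. The fertility calculation is already for the subgroup with pregnancy desire, so the two statements concern the same analysis. At stake is how a null fertility result is read. A reader who relies on the Sample size section would take it as evidence from an adequately powered comparison. A reader who relies on the limitations would not.

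**Working it through.** **Inputs, all from the Sample size section.** Fertility: p1 = 0.48 (range 0.37 to 0.55), p2 = 0.15, two-sided α = 0.05, power 0.80, loss 10%. Primary: 0.5525 vs 0.715, same α, power above 0.80, loss 5%. Allocation is 1:1 (Study design).

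**Formula (arcsine).** n per group = 2 × [(z₀.₉₇₅ + z₀.₈₀) / h]², with h = 2·asin√p1 − 2·asin√p2 in absolute value and z₀.₉₇₅ + z₀.₈₀ = 1.960 + 0.842 = 2.802.

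**Primary figure first.** n = 136.36, so 137 evaluable. 136.36 / 0.95 = 143.5, so 144. The stated 144 is reproduced as the number *after* loss. Had 144 been the evaluable number, adding 5% loss would give 144 / 0.95 = 151.6, so 152, which the plan does not do.

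**Fertility figure.** h = 1.5308 − 0.7954 = 0.7354, so n = 2 × (2.802 / 0.7354)² = 29.03, so 30 evaluable per group. The stated 33 is not reproduced at this step.

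- With loss: 29.03 / 0.90 = 32.25, so 33.
- Loss again: 33 / 0.90 = 36.7, so 37.

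The result depends on how loss is applied. Dividing the unrounded n gives 33 and 144. Rounding first and multiplying gives the same pair (30 × 1.10 = 33; 137 × 1.05 = 143.85, so 144). Rounding first and dividing gives 34 and 145 (30 / 0.90 = 33.3; 137 / 0.95 = 144.2). Any convention that reproduces 144 with one loss allowance also reproduces 33 with one.

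**Other formulas without loss, fertility inputs:**

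| Formula | n per group |
|---|---|
| Unpooled variance | 28 |
| Arcsine | 30 |
| Pooled (usual two-proportion) | 30 |
| Single pooled variance | 32 |
| Arcsine, continuity-corrected | 35 |
| Pooled, continuity-corrected | 36 |

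None of these gives 33.

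**Power at 48% vs 15%** (h·√(n/2) − 1.960 referred to the normal distribution for arcsine; the pooled formula for comparison):

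| Evaluable per group | Arcsine | Pooled |
|---|---|---|
| 30 | 81% | 80% |
| 33 | 85% | 84% |
| 37 | 89% | 88% |

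**Dependence on subgroup size.** The article does not give the expected share of women with pregnancy desire, so the totals of 40, 50 and 60 below are assumptions. Evaluable per group = total / 2 × 0.90.

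| Women randomised | Evaluable per group | Power (pooled to arcsine) |
|---|---|---|
| 40 | 18 | 57–60% |
| 50 | 22.5 | 67–69% |
| 60 | 27 | 76–77% |
| 74 | 33.3 | 84–85% |

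The target of 74 is 74 / 288 = 25.7% of the trial.

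**Dependence on the effect.** At the lower end of the article's range for sclerotherapy (37% vs 15%), 33 evaluable per group give 53% (pooled) to 55% (arcsine), and 80% power would need 60 (arcsine) to 62 (pooled) per group. At the upper end (55% vs 15%), 33 per group give 94% (pooled).

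**The case against.** **The double loss is an inference.** The article never says that 33 includes loss. The sentence naming the arcsine method closes the primary paragraph, and the fertility paragraph names no method. A t-approximation with a single pooled variance gives 32.09, hence 33 without any loss, though that would be an unusual choice. This stands as far as it goes: the right word is *appears*. The inference is still strong, because one explanation reproduces 33, 37 and 144 together. Even without it, 33 is not what the only named method gives.

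**The error does no harm.** This stands. A second loss allowance raises the target. A reader might infer that the fertility comparison is underpowered as planned, or that the target should fall to 66 or 68. Neither follows: 74 women give more than the stated 80% under the stated effect, and nothing is gained by recruiting fewer.

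**A calculation and a caution can coexist.** A sample size is always conditional on its assumptions, and the limitation openly warns readers. That would settle the matter if the closing sentence were conditional. It is not.

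**Recruitment to the subgroup may be controlled elsewhere.** A reader might infer that no quota exists or that 74 will not be reached. The article does not show this. It calls 74 a target, and a full protocol could hold the recruitment detail. What the article does show is that stratification balances the arms and does not fix the size of the subgroup.

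**Choice of test.** The Statistical analysis section allows χ² or Fisher's exact test for categorical outcomes, and exact power with 33 per group is about 77% under Fisher. A reader might conclude that the plan must prescribe χ². The article does not support that: the choice may be settled in the unseen analysis plan, and with about 10 expected pregnancies per arm (33 × (0.48 + 0.15) / 2 = 10.4) a small-count rule would rarely call for Fisher.

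**Conclusion.** The point holds and is minor. The stated 33 per group at 80% power is not the arcsine result, which is 30. It matches that result after 10% loss, so the loss appears to be applied twice on the way to 37, while the primary 144 appears to carry its loss once. The consequence is conservative: with 74 women and 10% loss, power is about 85% rather than 80%. This rests on the arcsine sentence covering both paragraphs.

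The conflict over power is documented within the article and matters more for interpretation. Adequate power for reproductive outcomes holds only if enough women with pregnancy desire are enrolled and the difference is near 33 points. The 40-, 50- and 60-woman scenarios illustrate this dependence and are not forecasts. The 37% vs 15% case is sensitivity to the article's own range and is not itself an error. The primary endpoint's sample size is not affected by this point.

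**What to change.** In the Sample size section:

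1. State that 30 evaluable women per group give 80% power for 48% vs 15% by the arcsine method, and say that this method applies to both calculations.
2. Show loss once and in the same way in both paragraphs: the evaluable number first, then the number to randomise. For the primary endpoint, say that 144 already includes the 5% loss.
3. Keep the target of 74 women and describe it as giving about 85% power after 10% loss under the stated effect.
4. Replace the unconditional closing claim with a conditional one, for example: *Power for reproductive outcomes is about 85% if 74 women with pregnancy desire are randomised, 10% are lost and the true rates are 48% and 15%; with fewer such women or a smaller difference it is lower.*
5. Align the Strengths and limitations section with that sentence.

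The cost is wording only. No target, recruitment figure or analysis changes. If 33 came from another formula without loss, the sponsor should name that formula; items 4 and 5 are still needed.
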